#### 2.3.4. Participant Blinding

This will be a double-blind study with both the trial participants and researchers/care staff responsible for data collection and analysis (MCRF staff; [name]; and [name]) blinded to the exposure. Other investigators will not be blinded as to the order of exposures. Participants will be informed about the five pollution exposures, but the sequence in which they encountered them will remain undisclosed. To assess potential unblinding among trial participants, the (unblinded) MAC team will ask participants to indicate which of the five exposures, including clean air, they believe they encountered following each one-hour exposure. Furthermore, participants will be asked to provide a confidence judgment along with their response. Trial participants and data collection staff will also be blinded during data analysis.

The PI will make the decision to un-blind the current participant exposure in the case of a serious adverse event (SAE) when knowledge of the chemical composition of the exposure is vital for appropriate clinical management or the participant’s well-being.

While there is a risk of unblinding due to smell, adding scents to mask pollutants or using external agents like menthol nasal rubs poses separate challenges, including potential alterations in the pollutant mixture and their impact on airway dilation, introducing additional confounding factors.

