The study is designed to attempt to discriminate between the responses to exposure to 4 common pollutant types and a clean air control. The pollutant types have been selected as they make significant contributions to ambient air quality in indoor and outdoor situations. It is not possible to conduct exposures to emissions generated under all possible operating conditions of the individual sources. However, selection of a set of standard operating conditions for each source enabling the stable and repeatable generation of each pollutant emission type can enable comparison of the responses to exposure to each of the classes of pollutant. A description of the standard operating procedures and the chemical and physical characterisation of each source is the subject of a manuscript in preparation.

Participant exposures will be conducted at the Manchester Aerosol Chamber (MAC) facility. The MAC facility is part of the ATMO-ACCESS atmospheric simulation chamber network. It is an 18 m^3^ fluorinated ethylene propylene Teflon bag housed in a temperature- and humidity-controlled enclosure and illuminated by a combination of wavelength-filtered arc and halogen lamps. Clean inlet air is ensured by scrubbing with a series of filters and conditioners. Particle and gas levels are controlled either by injection of individual components or by coupling to a variety of real pollutant sources [49]. This facility as well as the techniques and specific instruments employed here have been used in many previous chamber studies [50,51,52]. For each pollutant mixture, a full characterisation will be conducted to identify the exact chamber conditions and experimental setpoints to achieve target pollutant concentrations to within acceptable limit. All experimental setpoints are computer-controlled and continuously monitored, ensuring participant safety, and enabling repeatability.

The aim is to achieve desirable PM (particle matter) mass concentrations (150 
μ
g m^−3^) for human exposure studies. The chemical and physical characterisation of particle and gas phase pollutants from each source was conducted using online instruments, and a protocol has been developed for generating desirable and reproducible PM mass concentrations from each source. Detailed information on this process is the subject of a manuscript in preparation. A brief description is provided below.

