### 2.7. Data Analysis

Data generated by this study will be analysed using longitudinal statistical modelling designed to account for the repeat measures in individual subjects (e.g., general estimating equation or random effects modelling, depending on the extent and nature of any missing or partial data). This will describe and account for changes in pre-exposure measures over time, comparing the effects of the different air pollution exposures to the clean air control.

Cognitive subscales will be entered into this process separately, to aid in pairing aerosols with undesirable changes identified in each cognitive domain. Our goal is to ensure an equal representation of biologically male and female participants, acknowledging potential sex-dependent effects of exposure. Consequently, biological sex will be entered as a covariate of interest during analysis.

In addition to ranking cognitive impacts in relation to the exposure sources, these data will be related to biomarkers of systemic and neuro-inflammation/injury to test the secondary hypothesis that acute cognitive effects and more severe downstream neurological impacts reflect underlying inflammatory processes.

Specifically, our primary and secondary end points are as follows:

Primary end point:

Evidence of impairment in cognitive function post exposure as measured by any of these cognitive tasks compared to clean air:Difference in the Approach bias measured via the Expression Recognition Task post pollutant exposure;Change in the Cognitive Control response time post pollutant exposure;Change in the 2-back discrimination index post pollutant exposure.

Secondary end point:

Change in performance on any of these cognitive tasks post pollutant exposure compared to clean air:Psychomotor Vigilance Task;Purdue Pegboard Test;Evidence of inflammatory or immune signals post exposure to pollutants compared to clean air;Change in lung function post pollutant exposure compared to clean air;Change in DNA post pollutant exposure compared to clean air.

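### Unblinded chamber staff ask participants to name their exposure after each session, which may cue the guess and, if asked before the cognitive tests, may add expectancy to the primary outcomes

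*Protocol article*

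**What the plan says.** Section 2.3.4 of the protocol article describes the trial as double-blind. Participants are blinded, and so are the "researchers/care staff responsible for data collection and analysis", who include the clinical research facility staff. Other investigators are not. On what participants know, the section says: "Participants will be informed about the five pollution exposures, but the sequence in which they encountered them will remain undisclosed".

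The blinding check is set out in the same section. The document states that "the (unblinded) MAC team will ask participants to indicate which of the five exposures, including clean air, they believe they encountered". The timing is given only by the words "they believe they encountered following each one-hour exposure". In addition, "participants will be asked to provide a confidence judgment along with their response".

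The section concedes one route to unblinding ("While there is a risk of unblinding due to smell") and gives reasons for not masking odours. Section 2.4 fixes the place: "Participant exposures will be conducted at the Manchester Aerosol Chamber (MAC) facility". Section 2.1 puts cognitive testing before and after each exposure. The primary end point in section 2.7 is "Evidence of impairment in cognitive function post exposure as measured by any of these cognitive tasks compared to clean air", measured by approach bias, cognitive control response time and the 2-back discrimination index.

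**The concern.** Two things are at stake, and they do not depend on the same facts.

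The first is the blinding check. A participant who is asked to choose among five exposures by someone who knows the right answer can pick up tone, hesitation or other unintended cues. A correct guess may then reflect smell, a cue from the asker, or both. The check is the trial's stated means of judging whether participants were unblinded, so its result should not be open to that doubt.

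The second is the primary outcome. All three primary measures are performance tasks that depend on effort and attention. If a participant has just had to settle on a label such as diesel or clean air, and say how sure they are, any expectation attached to that label may be stronger when the tests begin. This applies only if the question precedes the tests.

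**Working it through.** The document gives no figure for this point, so the check is mainly a comparison of sections.

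**1. Who asks.** Section 2.3.4 names the chamber team and labels it unblinded. It mentions no blinded asker and no self-completed form. The possibility of cueing therefore follows from what the text fixes, not from a gap in it.

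**2. What cueing does to the check.** There are five options, so uniform guessing without any information or elimination gives 1/5 = 20% correct. An excess over 20% would be read as unblinding. When the asker knows the answer, that excess mixes what the participant inferred unaided with what the asker conveyed. The two cannot be separated afterwards.

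**3. When the question is asked.**
- It is tied to the end of the one-hour exposure (section 2.3.4).
- It is put by the team that runs the chamber, where exposure takes place (sections 2.3.4 and 2.4).
- Blinded staff collect the outcome data (section 2.3.4), and cognitive tests follow exposure (section 2.1).

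Taken together, these most naturally place the question at the chamber, before testing. No sentence says so. Figure 1, which shows the procedure, is not available here. Table 1 gives each exposure a Visit A and a Visit B, and section 2.5.2 takes the second set of blood samples on visit B. The interval between question and tests is therefore unknown.

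**4. How long a later guess would be delayed.** Table 2 gives task durations of 10 + 15 + 10 + 15 + 10 = 60 minutes. Moving the guess to the end of the battery delays it by at least about an hour, and by more if the battery is not run straight after exposure.

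**5. Can the expectancy effect be sized?** Only as an illustration. Assume that belief alone shifts response time against clean air by 2.5, 5 or 10 ms. Borrow the SD of 25 ms from section 2.3.1 and treat it as the SD of a paired contrast. For a two-sided paired t test at 0.05 with n − 1 degrees of freedom, the noncentrality is (shift / 25) × √n. The discussion gives 15 recruited with 33% dropout, so 15 × 0.67 ≈ 10 completers.

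| Assumed shift | Noncentrality, n = 10 | Chance of p < 0.05, n = 10 | Noncentrality, n = 15 | Chance of p < 0.05, n = 15 |
|---|---|---|---|---|
| 2.5 ms | 0.32 | 5.9% | 0.39 | 6.5% |
| 5 ms | 0.63 | 8.8% | 0.77 | 11.2% |
| 10 ms | 1.26 | 20.5% | 1.55 | 30.3% |

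The table describes expectancy from all sources, smell included. It does not describe the increment caused by asking the question, and nothing in the document supplies that increment.

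**The case against.** **The order is not stated.** This is correct. The figure or the full protocol may show the guess after testing. The expectancy part of the point is conditional for that reason. The cueing part is not affected.

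**Expectancy exists without the question.** This is also correct. Participants know the list and may recognise a source by smell. Asking can only add to that, and moving the question does not remove the smell problem.

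**The present arrangement has merits.** It does. A guess taken before testing is not coloured by how well the participant thinks they performed. Having the chamber team ask also keeps the guesses away from blinded data collectors. A sealed form keeps the second merit. The first is given up if the form is completed after the battery.

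**Stronger readings the document does not support.**
- A reader might take the table above as the inflation in false positives caused by asking. The shifts are assumed and cannot be assigned to the question rather than to smell. The SD comes from a study that section 2.3.1 itself says had an independent design and could not be extrapolated. It also relates to response time, and so to only one of the three primary measures.
- A reader might infer that expectancy moves every primary contrast the same way. The document does not say that all four pollutants smell or that clean air is odourless. It gives approach bias no direction. A shift common to all four pollutants would also cancel when they are ranked against each other, which is the primary objective.
- A reader might infer that the guesses will serve only to describe unblinding. Their use in analysis may be set out in an analysis plan that is not shown.
- A reader might want to discount any contrast that disappears after adjustment for believed exposure. If smell reveals the source, belief is nearly collinear with true exposure. With 10 to 15 participants, such an adjustment could remove a real effect.

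**Conclusion.** The point holds in a limited form. As written, the blinding check is put to participants by staff who know the answer. This weakens the check and rests on the stated text alone. The further risk, that the question reinforces expectancy on the primary outcomes, depends on the question preceding the post-exposure tests. That order is likely from the wording but not established. The added effect has no size that can be derived from the document. The point does not show that the primary results are biased. It identifies an avoidable weakness in a stated procedure that is cheap to remove.

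**What to change.** - Collect the guess and the confidence rating on a form that the participant completes alone and returns sealed. Unblinded staff then do not elicit it, and blinded data collectors do not see it.
- Preferably have it completed after that session's post-exposure cognitive battery, and state the order in the protocol.
- For sessions already completed, report the order that was used. Section 2.3 expected data collection to end in 2023, so this may be the main action still open.
- Keep any analysis by believed exposure descriptive or exploratory. It should not serve as a rule for attributing or discarding pollutant effects.

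The cost is one short form and a change in the order of one question. Exposures and outcome measures are untouched. The price of the later timing is a guess given at least about an hour after exposure, which perceived performance may colour. If that is judged worse than the expectancy risk, the sealed form is still worth adopting at the present time point.

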#### 2.3.5. Participant Safety and Anonymity

All participants enrolled in this study will be allocated a unique anonymous identifying code which will appear on all data collection documents. The hard-copy case report forms (hCRF) and source data files (SDF) will be kept within a locked room. All electronic data will be stored on secure password-protected servers with limited access to members of the research team.

Participant eligibility will be reviewed at the beginning of each visit (separated by a minimum two-week washout period) prior to air pollution exposure. Participation will be discontinued for those who do not match the eligibility criteria when reviewed.

The checking for the occurrence of adverse events (AEs) will begin from enrolment and will continue for the individual participant until their last visit. At each study visit, the researcher will assess eligibility and recent clinical history including the occurrence of adverse or serious adverse events (SAEs). Details of adverse and clinical events will be captured on the trial hCRF and eCRF. All SAEs will be recorded in the hospital notes, the eCRF, the hCRF, and the Sponsor’s SAE Recording Log. All SAEs will be reported to the Sponsor via the Research Office (RO) dedicated mailbox on an SAE form and the SAE Log will be sent to Sponsor on request. The PI will complete the Sponsor’s SAE form and the form will be sent within 24 hours of the Investigator becoming aware of the event. The PI will respond to any SAE queries raised by the Sponsor as soon as possible.

Expected Adverse Reactions are possible short-term respiratory symptoms such as cough/shortness of breath to susceptible individuals. We will minimise this risk by assessing the participants pre-enrolment onto the study for respiratory conditions. We will also conduct safety measures such as spirometry and exclude individuals with abnormal results which may also suggest a high risk to pollutant exposure. Investigators will complete the appropriate SAE form on the eCRF and an automatic email notification will be sent to the Trial Manager, PI and Sponsor.

A Suspected Unexpected Serious Adverse Reaction (SUSAR) is an adverse reaction that is classed as both serious and unexpected. The Trial Manager will ensure that SUSAR reports are un-blinded and reviewed by the PI or designee within 2 days and adjudicate whether the event constitutes a SUSAR. The Trial Manager will ensure that fatal or life-threatening SUSARs are reported to UREC as soon as possible, but no later than 7 calendar days after the receipt of the eSAE report. Any additional information will be reported within 8 days of sending the first report.

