#### 2.3.1. Power Calculation

Based on effect size and variance from a currently unpublished study [35] looking at cognitive load and attention (measured as change in response time (
Δ
RT) after Diesel Exhaust exposure (
Δ
RT = 22 ms, s.d. = 25 ms), a sample size of 30 subjects will have 90% power to detect significant response time changes of 15 ms assuming the standard significance level of *p* < 0.05. We acknowledge this current study is a different design utilising an older adult population and have, therefore, calculated for a slightly smaller effect size than that of the previous study to compensate for larger RT variance in older adults. As longitudinal studies are prone to extensive participant attrition, the sample size of 45 aims to allow full data to be collected for a minimum of 30 participants. Power calculations were performed using PS [36].

In response to recruitment challenges, we revised the sample size, prompting a re-exploration of the sample size estimate and power calculation to identify the minimum sample likely to yield valuable results. The proposed study design involves comparing the impact of four pollution exposures by examining the differences between pre- and post-exposure measurements relative to baseline measurements. The independent design from the previous study, featuring one measure per group, makes it unfeasible to extrapolate data. Therefore, under the assumption of a conservative correlation among repeated measures set at 0.5, a minimum sample size of 11 participants is needed to achieve 90% power in detecting a moderate (0.45) effect size at a significance level of 0.05.

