#### 2.3.3. Recruitment

Participants will be recruited from the general public. Volunteers who are employees of The University of Manchester or Manchester University NHS Foundation Trust will be permitted to take part if not involved with the project. Advertisement posters will be placed in public spaces including local community groups, places of worship, and NHS and university buildings. Social media advertisements will be run using official accounts of the University of Manchester, NHS Manchester Foundation Trust, and Research for the Future. We will also contact participants who have previously given permission to be contacted for research studies. Due to potential sex-dependent effects of aerosol exposure, we aim to collect equal numbers of biologically male and female participants.

To promote participant retention, participant payment will increase each visit so that there is an increasing incentive to continue participation as the study continues. Informal participant feedback will be collected each visit to improve subsequent visit comfort and amend the protocol as necessary. Data from those who discontinue participation, whether through personal withdrawal or change in eligibility, will be included in data analysis where inclusion of partial data is possible.

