## Appendix A. Inclusion and Exclusion Criteria

The study inclusion criteria are:

- Age ≥ 50 years of age;
- Family history of dementia (first- or second-degree relative);
- Provision of signed, written, and dated informed consent, prior to any study specific procedures.

Participants will be excluded if any of the following criteria apply:

- Neurological or psychiatric disorder;
- General Practitioner Assessment of Cognition Score of ≤ 7;
- Current smoker (including e-cigarettes) or ex-smoker of less than 6 months abstinence, and < 20-pack/year history;
- Current pregnancy;
- Significantly abnormal spirometry;
- History of cardiac disease;
- History of chronic respiratory or airways disease;
- History of inflammatory diseases (e.g., rheumatoid arthritis, chronic periodontitis, inflammatory bowel disease);
- History of neurological or psychiatric disorders;
- History of organ transplant;
- Consumption of >3 units of alcohol in the 24 h preceding testing visit;
- Any vaccination in the week prior to the testing visit;
- Cold or flu in the 48 h prior to the testing visit;
- Visual impairment not correctable with glasses/contact lenses;
- Significant claustrophobia preventing the participant from wearing a mask over the nose and mouth for an hour;
- Concomitant medication use of neurologically active drugs such as opiates/ benzodiazepines/anti-epileptics, etc.;
- Substance misuse.

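### Section 2.3.5 ends participation for any failed eligibility review, with no exception for three passing, visit-level states in Appendix A (minor)

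*Protocol article*

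**What the plan says.** Section 2.3.5 sets the timing of the check: "Participant eligibility will be reviewed at the beginning of each visit (separated by a minimum two-week washout period) prior to air pollution exposure". The next sentence gives the only stated consequence of failing it: "Participation will be discontinued for those who do not match the eligibility criteria when reviewed".

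Appendix A has a single exclusion list. Among lasting conditions such as organ transplant and chronic respiratory disease it includes three short-lived states, each tied to the testing visit. One concerns recent alcohol: "Consumption of >3 units of alcohol in the 24 h preceding testing visit". A second is having been vaccinated at any time during the previous seven days. The third concerns a recent respiratory infection: "Cold or flu in the 48 h prior to the testing visit".

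Section 2.3.3 groups loss of eligibility with personal withdrawal and keeps the partial data where possible: "Data from those who discontinue participation, whether through personal withdrawal or change in eligibility, will be included in data analysis". Section 2.7 would analyse them by "general estimating equation or random effects modelling, depending on the extent and nature of any missing or partial data".

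Table 1 marks an eligibility screen in every exposure period. It ends with a Remnant Exp(s) period, 20 to 30 November 2023, marked for Visits A and B of all five exposures and for the eligibility screen. The article does not say which absences that period is meant to cover.

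**The concern.** The rule makes no distinction between a participant who has become permanently unsuitable and one who has a cold that day. Someone in the second group could be tested safely a week or so later. Under the sentence as written, that person leaves the study and every remaining exposure is lost.

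Each participant is meant to supply all five conditions, and the recruitment target has already been cut from 45 to 15 (Sections 2.3 and 3). Sessions lost to a passing state are therefore worth avoiding. The rule also works against the article's own retention effort, in which payment rises with each visit (Section 2.3.3).

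**Working it through.** **1. Does the text allow postponement?** Section 2.3.5 has no qualifier, Appendix A has no separate list of reasons to defer, and Section 2.3.3 treats a change in eligibility as a way of leaving. Pointing the other way, the three criteria are worded by visit, and Table 1 has a catch-up period with its own eligibility screen. The article never connects the two.

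**2. Sessions lost.** Failing at session k of 5 under the literal rule loses 6 − k sessions: 4, 3, 2 or 1 for k = 2, 3, 4, 5. Postponing loses none, or one if no date can be found.

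**3. Effect on precision.** The plan gives no figure for this, so there is none to reproduce. Inputs: N = 15 (Section 2.3); five conditions (Section 2.1); correlation 0.5 (Section 2.3.1: "under the assumption of a conservative correlation among repeated measures set at 0.5"). Assumptions added here: one outcome per session, equal correlation between sessions, 14 complete participants plus one truncated, and every exposure order equally likely.

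With V = (1 − ρ)I + ρJ, the generalised least squares information is the sum over participants of X′V⁻¹X. Results are ratios to 15 complete participants.

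- *Neither condition of the contrast was reached.* The participant adds nothing to that contrast: 15/14 = 1.0714. This is the upper limit.
- *Both conditions were completed before the failure.* Ratio 1.000, no loss.
- *Failure at session 2, one of the two conditions done.* (15/14) × [1 − (1 − ρ)/(2 × 15)] = 1.0714 × (1 − 0.25/15) = 1.0536.
- *Average for session 2.* The single completed session is one of the two conditions with probability 2/5: 0.4 × 1.0536 + 0.6 × 1.0714 = 1.0643.
- *Average for session 5.* Only the last condition is missing. The ratio is 1.0429 if it belongs to the contrast (probability 2/5) and 1.000 otherwise: 0.4 × 1.0429 + 0.6 × 1.000 = 1.017.

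Averaging over all 120 orders and the four pollutant-minus-clean-air contrasts:

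| Failure at session | Sessions lost | Mean variance ratio | Interval width (square root) | Range for a single contrast |
|---|---|---|---|---|
| 2 | 4 | 1.0643 | +3.2% | 5.4% to 7.1% |
| 3 | 3 | 1.0500 | +2.5% | 0% to 7.1% |
| 4 | 2 | 1.0339 | +1.7% | 0% to 7.1% |
| 5 | 1 | 1.0171 | +0.9% | 0% to 4.3% |

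Losing only the affected session gives a mean ratio of 1.0171 whichever session it is; postponing it gives 1.000. For session 2, correlations of 0.3, 0.7 and 0.8 give 1.0614, 1.0671 and 1.0686, so the result depends little on the correlation.

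**4. Is there calendar room?** From Table 1:

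- Each of the five main windows runs Monday to Friday over 19 days. A session due on one of the first 12 days (19 − 7) can move a week later and stay inside its window. A third-week session, or one in the five-day Exp 1 window for wave 2, would go to the Remnant period.
- The gaps from the end of one window to the start of the next are 17, 17, 10, 17, 17 and 17 days. All but one exceed the 14-day washout.
- The exception is wave 2 between Exp 3 and Exp 1 (11 to 21 August). An Exp 3 session held on 8 to 11 August needs an Exp 1 date 14 days later, 22 to 25 August, which is still inside that window.
- The Remnant period spans 11 days, less than the washout, so it holds at most one session per participant.

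**5. Where postponement does not work.** Each exposure has a Visit A and a Visit B, and the second blood sample is taken at Visit B (Section 2.5.2). If a cold starts after the exposure, the session cannot be put off without exposing the participant again.

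**The case against.** The strongest reply is that the article itself points to a harmless reading. A catch-up period with its own eligibility screen makes little sense if missed sessions are never made up, and a change in eligibility more naturally means a new diagnosis than a cold. The article also condenses a fuller protocol (version 1.6) that is not shown, and visit-day rescheduling is the kind of detail such an article leaves out. This stands in part: postponement may well have been intended. It does not remove the point, because the article does more than stay silent. It states a consequence, and that consequence conflicts with the benign reading.

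The reply on size also stands. No failure rate is given, and such losses may already lie within the assumed 33% dropout. Partial data are kept and modelled. A participant without a clean-air session still informs comparisons between pollutants.

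The averages rest on a random order that the article does not state. Table 1 places wave 2's Exp 1 after Exp 3, so the numbering may denote fixed exposures. The range for a single contrast is then the safer figure.

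Table 1 shows calendar room only. Chamber capacity is not given, and a source may have to be set up again. The practical scope is limited too: data collection was due to finish in 2023 and analysis to start in January 2024, before the article appeared.

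A reader might go further and infer that the rule will remove a substantial share of the 15, or take the trial below its stated minimum of 11. The documents do not support that. Any head count would need an invented rate of temporary ineligibility, and whether 15 less 33% reaches 11 is a separate question that does not depend on this rule. Nor do the documents show that anyone was discontinued for a temporary reason.

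**Conclusion.** The point holds as a minor one. Section 2.3.5 states an unqualified rule that, if followed, gives up sessions that could be recovered; if it was not followed, the sentence misdescribes the study. The same edit corrects either case.

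Per event, the variance of a pollutant-minus-clean-air contrast rises by 1.7% to 6.4% on average for a failure at sessions 5 to 2, and by 0% to 7.1% for a single contrast. This assumes 15 participants with the other 14 complete and equal correlation of 0.5; the averages further assume random order. The trial-level loss cannot be stated, because the frequency is unknown. The calculation concerns precision only and is no evidence of bias or of a changed error rate.

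**What to change.** In Section 2.3.5, limit discontinuation to lasting ineligibility and treat the three visit-level criteria separately:

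- **Found before exposure:** postpone the whole session, Visits A and B together, within the same window or to the Remnant period, subject to chamber availability and the two-week washout. Analyse it under its actual order.
- **Arising after exposure, at Visit B:** keep the participant, flag or omit the affected Visit B measurements, and continue with later sessions.

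If sessions were in fact postponed, correct the sentence to say so. If data collection has ended, report how many participants were discontinued for a temporary reason and at which session.

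The change takes a few sentences. Its costs are that some sessions move later, sources may need to be set up again, and actual order may differ from planned order for those participants. Nobody is exposed while ineligible.
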